# 4 STUDY DESIGN

## **4.1 OVERALL Design**

Aim 1 involves iterative testing and adaptation of the SD screening prototype using stakeholder-engagement and mixed methods. The screening prototype, which has been developed using stakeholder engagement in prior studies, will be implemented across patients as routine clinical care (consistent with national guidelines)^30,31^ in a single clinic (CHCO Neuro-Oncology). There will be 3-5 rounds of iterative testing, stakeholder feedback, and adaptation. This will occur until consensus is reached (described in detail under procedures).

Aims 2 and 3 involve a pilot, type 1, hybrid effectiveness-implementation trial using a pre-post design in 4 clinics. Pre-implementation effectiveness data will be collected via surveys in consenting/assenting patient participants. **Once Aim 1 has been completed, the study protocol will be amended to update intervention details prior to proceeding with implementation across all clinics as routine clinical care.**^30,31^ Following implementation of the screening approach, post-implementation data (effectiveness and implementation outcomes) will be collected via survey and EHR review in consenting/assenting patients. After effectiveness data collection is complete, implementation outcomes will also be assessed via surveys and interviews with consenting provider stakeholders.

*Overview of Project Methods, Participants, Timing and Data/Outcomes*

| **Aim/Years** | **Frameworks, Design**  **and/or Methods** | **Participants** | **Main Data/Outcomes** |
| --- | --- | --- | --- |
| Aim 1: Multistep Iterative SD Screening Approach Development  (Y1-2) | - Frameworks: RE-**AI**M, CFIR - Design: Iterative test/adaptation cycles, explanatory sequential mixed methods - Quantitative: patient and provider surveys - Qualitative: purposive interviewing, focus group | - Neuro-oncology patients ages 15-24 diagnosed with cancer - Neuro-oncology providers (physicians/PA/NP), nurses, and medical assistants (MAs) - Sites: Children’s Hospital Colorado (CHCO) Neuro-Oncology Program | - Finalized screening approach, materials and implementation plan to address barriers/facilitators identified and categorized using CFIR to promote adoption and implementation - Fidelity Checklist to be used in Aim 3 |
| Aim 2: Evaluation of Effectiveness of SD Screening Intervention  Y1 (Pre)  Y3-4 (Post) | - Framework: R**E**-AIM - Design: Type 1 hybrid effectiveness-implementation trial with pre-post design in 3 clinics - Quantitative: Patient surveys, electronic health record, chart review and referral extraction | - Oncology patients ages 15-24 diagnosed with cancer prior to age 18 years - Sites: CHCO HOPE Survivorship Program, CHCO Oncology Clinic, CHCO Neuro-Oncology Program, Seattle Children’s Cancer Survivor Program (SCH) | - Primary outcome: patient-reported SD conversation with a provider - Patient-level secondary outcomes: patient-reporting of SD needs, indication of needs met, patient satisfaction - Provider-level secondary exploratory outcomes: visits with documentation of SD screening, referral patterns |
| Aim 3: Evaluation of Implementation Outcomes and Factors  Y3-4  Y4 (after Aim 2 complete) | - Frameworks: **R**E-**AI**M, CFIR - Design: Type 1 hybrid effectiveness-implementation trial with pre-post design in 3 clinics, explanatory sequential mixed methods - Quantitative: Patient and provider surveys - Qualitative: Purposive qualitative interviews | - Oncology patients ages 15-24 diagnosed with cancer prior to age 18 years - Oncology/survivorship providers (physicians/PA/NP), nurses, and MAs - Sites: CHCO HOPE Survivorship Program, CHCO Oncology Clinic, CHCO Neuro-Oncology Program, Seattle Children’s Cancer Survivor Program (SCH) | - Measurement of reach, fidelity, adoption, acceptability, feasibility, and appropriateness - Exploration of factors affecting implementation to inform future scale-up |

## **4.2 SCIENTIFIC RATIONALE FOR STUDY DESIGN**

The goals of this proposal are to 1) create a feasible and acceptable SD screening approach and 2) develop an implementation package for further implementation and dissemination to effect change for more patients. Implementation science utilizes separate frameworks to evaluate different aspects of a study, including implementation outcomes and contextual factors that influence outcomes (Figure 1).^1,43-45^ This study will use iterative testing and adaptation using stakeholder engagement and mixed methods. The overall structure and outcomes of this proposal are guided by RE-AIM, with a focus on adoption and implementation planning.^46,47^ The Consolidated Framework for Implementation Research (CFIR) will be used in planning and evaluation to understand contextual factors (e.g. facilitators/barriers, in five multilevel domains; see Figure 1) that may influence RE-AIM domains, informing intervention adaptation and future implementation.^48,49^

[figure not shown]

**Implementation conditions, barriers, facilitators (why?)**

**Multilevel Dimensions**

- Intervention characteristics
- Outer setting
- Inner setting
- Characteristics of individuals
- Process

**Implementation outcomes (who, what, where, how, when?)**

**Individual-Level Dimensions**

- Reach
- Effectiveness
- Maintenance

**Setting-Level Dimensions**

- Adoption
- Implementation
- Maintenance

*Figure 2. Implementation planning conceptual framework: using RE-AIM and CFIR to plan for successful implementation (adapted from King 2020).^1^*

Our prior stakeholder-engaged research has resulted in a prototype screening approach that will be implemented across all eligible patients in a single clinic setting to adhere to national guideline recommendations for regular screening for sexual function concerns across the cancer care continuum.^30,31^ We will iteratively adapt our existing stakeholder-informed screening prototype in a real-world clinical setting through cyclical testing and adaptation (Aim 1). Then, we will broaden use of the screening intervention use a type 1, hybrid trial design (Aims 2-3) to simultaneously establish preliminary effectiveness and implementation outcomes of this screening approach. The type 1 hybrid design will facilitate future dissemination by testing the effects of the intervention while simultaneously identifying multilevel barriers and facilitators to real-world implementation.

## **4.3 end of study definition**

Aim 1

Based on recommendations in the literature, we expect that this process will require 3-5 rounds of iterative modifications addressing stakeholder feedback. Three stopping criteria will be used: (1) saturation in key informant interviews regarding identified barriers/facilitators (i.e., no new unaddressed barriers/facilitators identified); (2) at least 80% of each group of stakeholders (patient, medical) surveyed will have scores of 4 or higher on the modified AIM, FIM, and IAM surveys (indicating an average response of “agreeing” or “strongly agreeing” to items assessing the acceptability, feasibility, and appropriateness of the screening approach); and (3) stakeholders will identify no major problems with the screening approach (note that in the user-centered design field, “major problems” are defined as those which would severely limit the ability of end-users to implement the screening approach).

Once these stopping rules are met, the PI, mentors, and collaborators will produce a draft screening approach protocol and implementation package (e.g., use of a “clinical champion”, provider training, use of reminders in the electronic health record (EHR), flexibility for electronic or paper administration). If the stopping rules have not been met after 5 rounds, the research team will decide upon the draft screening approach protocol and implementation package based on feedback elicited through the 5th round. This will be presented for final feedback and modification at a medical stakeholder focus group.

Aim 2-3

Completion of data collection of effectiveness and implementation outcomes for the specified number of patients post-implementation of the sexual function screening tool.

# 5 STUDY POPULATION

## **5.1 patient Inclusion/Exclusion Criteria**

***ADAPTATION PHASE (Aim 1)***

**Inclusion Criteria**

In order to be eligible to participate in this study, an individual must meet all of the following criteria:

1. Provision to sign and date the consent or assent form.
2. Stated willingness to comply with all study procedures and be available for the duration of the study.
3. Be aged 15-24 years old at the time of enrollment
4. Patients with or surviving nervous system (CNS) cancers (must be found in the International Classification of Diseases for Oncology (ICD-O) and have a behavior code ≥2)
5. Must have received cancer-directed therapy with at least one of the following:
   - Chemotherapy: any anticancer drug to treat the cancer diagnosis including immunotherapy
   - Radiotherapy: any radiotherapy to treat the cancer diagnosis
   - Surgery: any surgery to remove cancer including partial or total resections. Biopsies are not considered surgery.
6. Underwent prototype sexual function screening intervention in clinic

**Exclusion Criteria**

An individual who meets any of the following criteria will be excluded from participation in this study:

1. Unable to read and speak English
2. Patients who did not receive cancer-directed therapy
3. Insufficient cognitive functioning to complete study measures, as determined by an oncology provider
4. Patient is at end of life or on hospice, as determined by an oncology provider

***HYBRID EFFECTIVENESS-IMPLEMENTATION PHASE (Aims 2-3)***

**Inclusion Criteria**

In order to be eligible to participate in this study, an individual must meet all of the following criteria:

1. Provision to sign and date the consent or assent form.
2. Stated willingness to comply with all study procedures and be available for the duration of the study.
3. Be aged 15-24 years old at the time of enrollment
4. Patients with or surviving of cancer (must be found in the International Classification of Diseases for Oncology (ICD-O) and have a behavior code ≥2)
5. Must have received cancer-directed therapy with at least one of the following:
   - Chemotherapy: any anticancer drug to treat the cancer diagnosis including immunotherapy
   - Radiotherapy: any radiotherapy to treat the cancer diagnosis
   - Surgery: any surgery to remove cancer including partial or total resections. Biopsies are not considered surgery.
6. Cancer must have been diagnosed before the age of 18 years
7. Patient must have an appointment at one of three clinical sites: CHCO HOPE Survivorship Program, CHCO Oncology Clinic, CHCO Neuro-Oncology Clinic, Seattle Children’s Hospital Survivorship Program

**Exclusion Criteria**

An individual who meets any of the following criteria will be excluded from participation in this study:

1. Unable to read and speak English
2. Patients who did not receive cancer-directed therapy
3. Insufficient cognitive functioning to complete study measures, as determined by an oncology provider Participation in Aim 1 intervention development
4. Patients who did not undergo SD screening within 1 month of being due will be excluded from implementation outcomes (Aim 3)
5. Patient is at end of life or on hospice, as determined by an oncology provider

Consent and assent will consist of paper or REDCap consent/assent with waiver of parental consent and HIPAA waiver for participants <18 years old.

## **5.2 medical stakeholder inclusion/Exclusion Criteria**

***ADAPTATION PHASE (Aim 1)***

**Inclusion Criteria**

In order to be eligible to participate in this study, an individual must meet all of the following criteria:

1. Provision to sign and date the consent form.
2. Stated willingness to comply with all study procedures and be available for the duration of the study.
3. Neuro-oncology providers, including physicians, nurse practitioners, physician assistants, registered nurses (RNs), and medical assistants (MAs) working in the Children's Hospital Colorado neuro-oncology clinic

***HYBRID EFFECTIVENESS-IMPLEMENTATION PHASE (Aim 3)***

**Inclusion Criteria**

In order to be eligible to participate in this study, an individual must meet all of the following criteria:

1. Provision to sign and date the consent form.
2. Stated willingness to comply with all study procedures and be available for the duration of the study.
3. Neuro-oncology, oncology, and survivorship providers, including physicians, nurse practitioners, physician assistants, registered nurses (RNs), and medical assistants (MAs) working at one of the study sites

*Of note, at sites where only certain providers are responsible for SD screening and/or follow-up, the full implementation assessment will be limited to these providers. However, non-responsible providers will also be included for brief acceptability interviews (see study design for details).*

## **5.3 SCREEN FAILURES**

Attempts will be made to screen for eligibility prior to obtaining consent/assent. However, if it is determined after consent/assent has been obtained that the patient is not eligible for any reason, the patient will be removed from the study.

Subject may be re-screened for eligibility with documented approval from the PI.

## **5.4 STRATEGIES FOR RECRUITMENT AND RETENTION**

As previously mentioned, the screening approach will be implemented as part of routine clinical care clinic-wide for patients ages 15-24 with or surviving cancer, adhering to national guidelines regarding sexual health and function clinical care.^30, 31^ Results of the sexual function screening tool will not be collected as part of research.

Research outcomes, as outlined above, will only be collected in consenting/assenting participants.

***ADAPTATION PHASE (AIM 1)***

*Surveys*: **Patient stakeholders** for surveys will be identified by study team; screening will occur through the PI and site PI’s clinical relationships with all patients (see section 10.1.1). Recruitment will occur on a rolling basis during existing clinic visits, or via phone within 4 weeks of the existing appointment, with purposive consecutive sampling to achieve variation across the age categories (age 15-19 and 20-24), patient treatment status (on therapy or survivor), and gender, with at least one member of each of these groups included in each round. Consent and assent will consist of paper or REDCap consent/assent with waiver of parental consent and HIPAA waiver for participants <18 years old (See section 10.1.1.2), presented in person or via email/MyChart/text after explanation of the study in person or over phone by research personnel. REDCap surveys will also be delivered in person or via email/MyChart/text after consent. With each round, after 3-5 patients have participated recruitment will be paused until any necessary modifications to the screening approach are made. Recruitment will resume once the modified approach is implemented. This will occur up to 5 times (n=9-25). **Medical stakeholder** recruitment in the screening approach development and/or the focused interviews will be performed by the research team, with all eligible stakeholders approached on a rolling basis, with purposeful sampling across all roles (provider, nurse, MA). REDCap postcard consent will precede data collection for medical stakeholders. Three to six medical stakeholder surveys will be administered with each round (n=9-30), with purposeful sampling to involve stakeholders of varying roles in the intervention and clinic in general. As compensation, all **stakeholder** survey participants will receive a $10 gift card per event if the local site allows provider incentives.

*Semistructured interviews:* Results of **medical stakeholder** surveys will be reviewed after each round. The research team will attempt to enroll a 1-3 medical stakeholders in each round for participation in a semistructured qualitative interview, first approaching the stakeholder who rated the intervention most critically (n=3-15). Informed consent will precede data collection. As compensation, all **medical stakeholder** interview participants will receive a $40 gift card per interview if the local site allows provider incentives.

*Field notes:* Research personnel will collect field notes to document observations and any additional (e.g., unsolicited or informal) feedback received from patients, families, or healthcare providers or other professionals in the practice environment. No identifiers will be included as part of field notes.

*Focus group*: After completion of the iterative testing and adaptation process, the final SD screening approach will be presented to a focus group of **medical stakeholders** (n=6; a least 1 each of provider, RN, and MA) (Appendix 4). These stakeholders will be recruited from all eligible stakeholders and informed consent will precede focus group participation. Participants will be compensated $40 gift card per focus group if the local site allows provider incentives.

***HYBRID EFFECTIVENESS-IMPLEMENTATION PHASE (Aims 2-3)***

*Pre-Implementation*: After eligibility screening (RA) and review (PI), **patient stakeholders** at each site (CHCO HOPE Survivorship, CHCO Oncology Clinic, CHCO Neuro-Oncology, Seattle Children’s Hospital [SCH] Cancer Survivorship Program) will be approached by research personnel at the end of each visit, or via phone within 4 weeks of the existing appointment, for participation in a survey (n=43). We will use a purposive consecutive sampling to achieve variation across the age categories (age 15-19 and 20-24), patient treatment status (on therapy or survivor), and gender, with final enrollment with a minimum 40% representation for each of these groups. Consent and assent will consist of a paper or REDCap consent/assent with waiver of parental consent and HIPAA waiver for participants <18 years old (when applicable – see section 10.1.1.2), presented in person or via email/MyChart/text after explanation of the study in person or over phone by research personnel. REDCap surveys will also be delivered in person or via email/MyChart/text after consent. Pre-intervention, the survey will assess SD communication and clinical care only (baseline effectiveness), and participation will be compensated with a $10 gift card.

*Post-Implementation:* The screening approach will be implemented across all eligible patients as part of clinical care. The research team will review eligibility of **patient stakeholders** through existing clinic schedules. Eligible patient stakeholders will be approached by research personnel at the end of each visit to present the study (prioritized), or by phone within 4 weeks of eligible visits (SD screening completed or overdue by 4 weeks or more), with a maximum of 3 attempts to reach potential participants. Study team members will be members of the Center for Cancer and Blood Disorder. Consenting/assenting participants completing the survey for data collection prior to leaving the clinic (preferred) or via REDCap emailed/MyChart/text link (n=43). We will again use a purposive consecutive sampling to achieve variation across the age categories (age 15-19 and 20-24), patient treatment status (on therapy or survivor), and gender, with final enrollment with a minimum 40% representation for each of these groups. Consent and assent will consist of a paper or REDCap consent/assent with waiver of parental consent and HIPAA waiver for participants <18 years old (when applicable – see section 10.1.1.2), presented in person or via email/MyChart/text after explanation of the study in person or over phone by research personnel. REDCap surveys will also be delivered in person or via email/MyChart/text after consent. Post-intervention, the survey will both effectiveness (all patients) and implementation (in those who received screening) (Aim 3, below); thus, participation will be compensated with a $20 gift card.

Research personnel will work with the study champions at each site to determine the best method to obtain **medical stakeholder** surveys (e.g., email, paper). Enrollment and consent of medical stakeholders will occur at the end of the post-implementation study phase, with all eligible medical stakeholders approached for participation in surveys (anticipating an 80% response rate, n=16-24). Medical stakeholders will receive $10 compensation for survey completion if the local site allows provider incentives. Medical stakeholder consent will be via REDCap postcard consent, with the opportunity to ask questions to research personnel.

*Semistructured interviews:* Results of medical stakeholder surveys will be reviewed to allow for purposive selection of medical stakeholders for interviews (n=10-15). Research personnel will intentionally approach medical stakeholders with a range of survey responses as well as proportional representation across roles and clinics. Medical stakeholders $40 for interview completion if the local site allows provider incentives. Medical stakeholder consent will be via REDCap postcard consent, with the opportunity to ask questions to research personnel.

# 6 STUDY INTERVENTION

## **6.1 Study INTERVENTION(S) ADMINISTRATION**

### **6.1.1 STUDY INTERVENTION DESCRIPTION**

This study is testing a standardized approach for sexual function screening, which is a part of recommended routine clinical care. The **prototype screening approach,** developed through our prior stakeholder engagement, will be adapted iteratively through stakeholder feedback in Aim 1 of this study. **Following completion of Aim 1, the study protocol will be amended as needed to include any relevant updates to the screening approach.**

The prototype screening approach will consist of:

1. Use of the PROMIS SexFS Brief across all patients ages 15-24 with or surviving cancer with a frequency of every 3 months or at next visit if seen less frequently than every 3 months; there will be a 1-month allowance/buffer from the date due to have screening completed. Flexibility of the intervention will allow each site will determine the appropriate modality to maximize patient privacy, comfort, and completion as well as adherence to HIPAA. Examples of components that may vary by site include modality of deliver (EHR, paper), timing of screening (before, during or after visit), results storage (EHR, paper), exact frequency of delivery, provider management (responsible providers, clinical resources).
2. Implementation approach: All sites will be provided with recommended strategies for implementation, which will be refined in Aim 1. Example strategies include use of provider education, clinical champions, EHR reminders, provider resources, and patient resources.

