| **Participating Sites:** | *Children’s Hospital Colorado Anschutz Neuro-Oncology Clinic (Aims 1-3), Children’s Hospital Colorado Oncology Clinic and HOPE Survivorship Program (Aims 2-3), Seattle Children’s Hospital survivorship clinic (Aims 2-3)* |
| **Description of Study Intervention:** | *The screening approach will consist of 1) Standardized use of the PROMIS SexFS Brief in a clinic setting and 2) An implementation package to aid in successful implementation.* |
| **Study Duration:** | *5 years* |
| **Participant Duration:** | *Patient stakeholders: 1 time completion of study surveys within 4 weeks of visit*  *Medical stakeholders:*  *Aim 1: 18 months*  *Aim 2-3: 1 time completion of study surveys and/or qualitative interview within 3 month of study completion* |

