**Data Collection/Outcomes*:***

*Effectiveness*: Data will be collected prospectively on patients during the 3-month pre-intervention phase (n=43) and patients who receive SD screening within 1 month of it being due during the 3-month post-intervention phase (n=43) (total n=86). Additional data will be collected EHR, including documentation of and referrals for SD. Participants will complete a survey (Appendix 5) at the end of scheduled visits or via phone within 4 weeks of screening completion. The **primary outcome** is a patient-reported indicator that his/her provider has communicated with them about SD. We anticipate that most providers will only address SD with patients who report a concern on the SexFS Brief; this assumption is reflected in sample size calculations. However, because our preliminary work demonstrated that patients wanted SD conversations to accompany the SexFS Brief, our analysis will include all patients, regardless of SD screening results. **Secondary outcomes**, detailed in section 3, include patient satisfaction with SD communication^51^ and patient-report that an SD need was met. We will also assess the feasibility of collecting EHR data in all eligible patients via retrospective chart review (exploratory outcomes):

- Clinic/site
- Incidence of documented/detected SD
- Referral patterns to SD-related specialty care (fertility team, urology, gynecology/oncology, sexual health clinic, endocrinology, etc.) via EHR order or note documentation **(exploratory outcomes)**.

These secondary and exploratory outcomes will inform a future multicenter trial defining the clinical impact of our screening intervention. Brief demographic data will also be collected for each participant.

*RE-AIM Outcomes:* Data will be collected using a combination of quantitative patient (Appendix 5) and medical provider surveys (Appendix 6) purposive qualitative interviews with medical stakeholders, and research personnel observation (Appendix 7 and 8).^2,52^ For sites that choose to have a limited number of providers responsible for survey delivery and follow-up/management, only responsible providers will receive complete surveys. Surveys will be administered in person by the RA. Interviews will be completed in person or via telephone by the study’s qualitative RA using CFIR interview guides, similar to Aim 1.^48^

Details on assessment:

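### The post-phase survey-timing rules conflict, so a patient at a site that screens after the visit can give the only primary-outcome survey before being screened and still count as screened.

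*Protocol*

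**What the plan says.** **When the screen may be given.** Section 6.1.1 lists, among components that may differ by site, "timing of screening (before, during or after visit), results storage (EHR, paper), exact frequency of delivery". It adds that "there will be a 1-month allowance/buffer from the date due to have screening completed".

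**How often the patient is surveyed.** The Synopsis (1.1, Participant Duration) specifies "1 time completion of study surveys within 4 weeks of visit".

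**When the post-phase survey is taken.** Four places address this:
- Section 5.4, Post-Implementation, gives priority to an approach at the end of the visit. The alternative is "or by phone within 4 weeks of eligible visits (SD screening completed or overdue by 4 weeks or more"). Participants are described as "completing the survey for data collection prior to leaving the clinic (preferred) or via REDCap emailed/MyChart/text link (n=43").
- Section 7.3 has surveys done at the visit straight after enrolment. It allows up to 4 weeks from an eligible visit, which it explains as one at which the screen is due.
- Section 8.1, Aims 2-3 Study Design, times the patient outcomes of the 43 post-phase patients within 1 month of a completed or overdue screen.
- Section 8.1, Effectiveness, says "Participants will complete a survey (Appendix 5) at the end of scheduled visits or via phone within 4 weeks of screening completion".

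**Who counts.** Section 8.1, Effectiveness, describes the post-phase sample as patients screened within 1 month of the due date. The primary outcome is the patient's report that a provider communicated with them about sexual dysfunction (SD).

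**The concern.** The primary comparison is meant to show whether screening leads to more SD conversations. That requires the post-phase answer to be given after the screen. The preferred survey route does not require this order, and the flexibility in 6.1.1 allows the reverse. Because there is one survey per patient, an answer given too early is never updated.

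A patient surveyed before the screen reports on a visit that the screening result could not have influenced. Counting that patient as screened pulls the post-phase proportion toward the pre-phase one. Since screening time is chosen by site, the dilution could also differ between sites and appear in the site-by-period interaction planned in 9.2.

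A narrower problem remains even if the screen always comes first. Section 8.1 expects most providers to raise SD only with patients who report a concern on the SexFS Brief. After an after-visit screen, the survey may be completed before any provider has seen the result.

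**Working it through.** **1. The rules side by side**

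| Place | Condition for the survey | Does the screen have to come first? |
|---|---|---|
| 5.4, in-clinic route (preferred) | End of visit | Not stated |
| 5.4, phone route | Screen completed, or overdue by 4 weeks or more | Yes, or a defined miss |
| 7.3 | Visit at which the screen is due | No |
| 8.1, Aims 2-3 Study Design | Within 1 month of completed or overdue | Completed, or overdue with no threshold |
| 8.1, Effectiveness, end of visit | None | Not stated |
| 8.1, Effectiveness, phone | Within 4 weeks of completion | Yes |

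**2. A sequence the text allows.** The screen is due on visit day 0 at a site that screens after the visit. The survey is completed at clinic exit on day 0 and the screen at home on day 7. The screen is inside the 1-month buffer, so the patient belongs to the post-phase sample in 8.1, with the outcome recorded 7 days before the screen.

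**3. The windows also disagree.** Take a screen due on day 0 and completed at the end of the buffer, about day 30. Section 8.1 allows the phone survey until day 30 + 28 = 58. The Synopsis closes the window at day 28. A patient whose screen was due on day 0 becomes overdue by 4 weeks on day 28, just as the Synopsis window ends.

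**4. The plan's sample size (9.2).** Inputs: p1 = 0.05, p2 = 0.30, two-sided alpha 0.05, power 80%, R² = 0.20 with the other predictors, 43 per period. The mean proportion is 0.175.

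n per period = [1.96·√(2·0.175·0.825) + 0.842·√(0.05·0.95 + 0.30·0.70)]² / 0.25² = 35.06

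Total = 2 × 35.06 / (1 − 0.20) = 87.6, against 86 stated. With 43 × 0.8 = 34.4 effective patients per period, power is 79.2%. The plan's figure is reproduced to within 2 patients and is not in dispute.

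**5. Sensitivity to early surveys.** Let f be the share of post-phase surveys answered before the screen, and r the rate at which those patients report a conversation.

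Expected post rate = (1 − f)·30% + f·r

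Neither f nor r is in the protocol. Setting r = 5%, the pre-period rate, gives 30% − 25f points:

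| f (assumed) | Post rate | Difference from 5% | Power at 43 per period, R² = 0.20 |
|---|---|---|---|
| 0 | 30.0% | 25.0 points | 79% |
| 10% | 27.5% | 22.5 points | 73% |
| 20% | 25.0% | 20.0 points | 65% |
| 30% | 22.5% | 17.5 points | 56% |
| 50% | 17.5% | 12.5 points | 37% |

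If provider training alone raised r to 15% (also an assumption), f = 20% would give 0.8 × 30% + 0.2 × 15% = 27% instead of 25%. The table is therefore the unfavourable end.

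**The case against.** The strongest reply is that the protocol already contains the gate. The parenthesis in 5.4 names a screen completed or overdue by at least 4 weeks, and the design text in 8.1 applies a similar condition to all 43 post-phase patients, not only to those phoned. Read as governing every approach, these would largely close the gap. This stands in part: a reader might infer that the protocol directs sites to survey before screening, and it does not. But the parenthesis sits in the phone clause, 7.3 defines an eligible visit differently, and 8.1 leaves the end-of-visit route unconditional.

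A reader might also infer that unscreened patients would be asked the Aim 3 acceptability, appropriateness, feasibility and fidelity items. The documents do not support that. Sections 5.4, 8.1 and 9.3 limit those items to patients who received the screen, and 5.1 excludes from Aim 3 those not screened within 1 month. What remains is that, at clinic exit, this status is not settled for a patient still inside the buffer.

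After-visit screening appears only as an example within a prototype, and 4.1 and 6.1.1 foresee an amendment after Aim 1. It may be that no site screens after the visit. That amendment, however, is described as covering the intervention, so survey timing would not necessarily be revisited.

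The size is assumed. Training, champions and reminders reach the whole clinic, and 9.2 itself expects some conversations whatever the screening result, so unscreened post-phase patients need not stay at 5%. This stands in full.

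Finally, an open-ended wait for provider follow-up would give only the post group more time for a conversation and would bias toward benefit. This also stands and limits the fix.

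**Conclusion.** The point holds as an unreconciled timing rule that permits the outcome to be recorded before the intervention. It rests on three things in the text: screening may follow the visit by up to the 1-month buffer, there is one survey, and the preferred survey route has no condition on the order.

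The direction of any bias is toward no effect, so it could hide a benefit but not create one. The size cannot be stated. The figure of 30% minus 25f points assumes both a share f and an unchanged 5% rate in those affected. It shows how quickly power would fall from 79%, not what will happen. A site-by-period distortion depends on the same unknown f. The sample size of 86 is sound on its own assumptions.

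The matter is worth settling before the post phase opens because it concerns the primary outcome and cannot be repaired once single surveys are collected.

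**What to change.** - Reconcile 5.4, 7.3 and both parts of 8.1 so that one gate applies to the in-clinic and remote routes: screen completed, or overdue by 4 weeks or more.
- Where the screen is not complete at clinic exit, take consent in clinic and release the REDCap link once the gate is met. Where it is complete, the end-of-visit survey stays as planned.
- Record the visit, screening and survey dates. Report how many surveys followed an after-visit screen with no provider contact in between. This makes the remaining gap visible without adding an open-ended wait.
- Keep the survey window and the reference period of the SD-communication question the same in the pre and post periods.
- Align the 4-week-from-visit limit in the Synopsis with the gate, since the two now meet or conflict when the buffer is used in full.

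Site freedom over screening time need not change. The cost is protocol wording, a REDCap trigger, and more remote surveys with somewhat lower response at sites that screen after the visit. Section 9.2 expects 0.5 × 38 × 3 = 57 participants against 43 needed. On those figures, response could fall to 43 / (38 × 3) = 38% before the target was missed in 3 months.
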